# Effectiveness of a community health worker-delivered care intervention for hypertension control in Uganda: study protocol for a stepped wedge, cluster randomized control trial

**DOI:** 10.1186/s13063-022-06403-9

**Published:** 2022-05-24

**Keywords:** Hypertension, Community health workers, Uncontrolled blood pressure, Cluster randomized control trial, Uganda

## Abstract

**Background:**

Over 80% of the morbidity and mortality related to non-communicable diseases (NCDs) occurs in low-income and middle-income countries (LMICs). Community health workers (CHWs) may improve disease control and medication adherence among patients with NCDs in LMICs, particularly in sub-Saharan African settings. In Uganda, and the majority of LMICs, management of uncontrolled hypertension remains limited in constrained health systems. Intervening at the primary care level, using CHWs to improve medical treatment outcomes has not been well studied. We aim to determine the effectiveness of a CHW-led intervention in blood pressure control among confirmed hypertensive patients and patient-related factors associated with uncontrolled hypertension.

**Methods:**

We will conduct a stepped-wedge cluster randomized controlled trial study of 869 adult patients with hypertension attending two NCD clinics to test the effectiveness, acceptability, and fidelity of a CHW-led intervention. The multi-component intervention will be centered on monthly household visits by trained CHWs for a period of 1 year, consisting of the following: (1) blood pressure and sugar monitoring, (2) BMI monitoring, (3) cardiovascular disease risk assessment, (4) using checklists to guide monitoring and referral to clinics, and (5) healthy lifestyle counseling and education. During home visits, CHWs will remind patients of follow-up visits. We will measure blood pressure at baseline and 3-monthly for the entire cohort. We will conduct individual-level mixed effects analyses of study data, adjusting for time and clustering by patient and community.

**Conclusion:**

The results of this study will inform community delivered HTN management across a range of LMIC settings.

**Trial registration:**

ClinicalTrials.govNCT05068505. Registered on October 6, 2021.

## Introduction

Non-communicable diseases (NCDs) represent a growing burden of morbidity and mortality, accounting for over 70% of the annual deaths worldwide. Over 80% of these deaths occur in low- and middle-income countries (LMICs) [1]. Hypertension is a serious medical condition and the major cause for premature death. The World Health Organization (WHO) estimates that globally 1.13 billion people suffer from hypertension, of which two thirds live in LMICs [2]. In 2015, on a global scale, one in four men and one in five women had hypertension. Fewer than one in five people suffering from hypertension have the disease under control [2]. Uncontrolled hypertension can result in significant morbidity including heart disease, stroke, vision changes, and hypertensive crisis, as well as premature death and increased costs of health care [2].

In Uganda, NCDs account for over 40% of the annual mortality [3]. In addition, more than a quarter of the Ugandan adult population has hypertension [4]. A study carried out in Uganda showed that only 9.4% of adults with hypertension had adequate blood pressure control and in urban and rural districts of Uganda over a fifth of persons aged 15 years and older suffer from uncontrolled hypertension [5, 6]. Hypertension control is crucial in reducing mortality and morbidity attributable to cardiovascular diseases. Furthermore, it is an important factor in lowering costs while using health care resources sustainably [7].

Inadequate control of blood pressure may be attributed to both provider-related and patient-related factors. Several studies imply that the primary patient-related factor is non-adherence with the prescribed antihypertensive medication. Therefore, the adoption of strategies that improve the long-term adherence to medication are recommended [8]. Among the factors which are associated with non-adherence are inadequate patient education towards disease management, high cost of medication and drug side effects. To overcome these obstacles in patient education and disease management, our study will test the effectiveness of a community health worker (CHW)-led intervention in rural Uganda.

CHWs are critical in bridging the gap in care between the community and the health centers. CHWs are usually community members who have completed a minimum of 7 years of education and are able to read and write in both English and Luganda. CHWs receive basic training on common health issues from the Ugandan Ministry of Health prior to being employed to the local communities where they support data collection and disease monitoring efforts. While working in a voluntary manner, they typically receive a small amount of monthly remuneration to support their work. They provide a link between the health sector and the communities [9]. CHWs are well utilized in the management of communicable diseases such as malaria, tuberculosis, and HIV [10, 11]. They have effectively provided a range of preventive and care interventions for maternal and child health and for infectious diseases in LMICs [12]. CHWs play an important role in ensuring that patients take their medications regularly and are additional a critical factor for improved patient survival [13]. A study in Uganda evaluated the care access and hypertension control in a CHW driven NCD program in rural Uganda. It indicates that hypertensive patients in a CHW program have a lower systolic blood pressure than the average systolic blood pressure of clinic patients [14]. Furthermore, a systematic review of sixteen trials that utilized CHWs for primary prevention and an early detection strategy in the management of NCDs in LMICs demonstrates that this strategy results in an increase in tobacco cessation and a decrease in systolic blood pressure, diastolic blood pressure, and blood sugar levels [15].

In Uganda, just like majority of LMICs, management of hypertension strains the already stretched health care delivery system. Evidence indicates that CHWs contribute positively to health care services as well as mortality and morbidity reduction. However, evidence on the role of CHWs in delivering interventions for NCDs on a primary care level is still developing and limited in Uganda and other LMICs [15, 16]. This lack of evidence is particularly the case for rural areas. Therefore, the purpose of this study is to evaluate the effectiveness of a community health worker-led intervention to control hypertension in rural Uganda.

## Design and methods

### Study setting

This study will be conducted in Nakaseke, Uganda, and coordinated by African Community Center for Social Sustainability (ACCESS). Since 2016, this research group along its international partners has established a network of CHWs trained in the identification and early diagnosis of NCDs such as hypertension, diabetes mellitus, chronic pulmonary obstructive disease (COPD), and kidney disease.

The study will be carried out in 102 villages within Nakaseke district. Study participants will be recruited from two NCD clinics within Nakaseke district: (i) Nakaseke hospital NCD clinic which is located in the general outpatient department of Nakaseke General Hospital and (ii) Life Care Center NCD clinic located at ACCESS which provide comprehensive NCD screening, care and management of patients. These clinics work closely with CHWs and are funded by Else Kröner-Fresenius-Stiftung and supported by Uganda’s Ministry of Health.

Three sub-counties have been selected for sampling of clusters. These include Nakaseke, Nakaseke Town Council, and Kasangombe. Sub-counties for sampling have been selected based on proximity to the two clinics as well as urban and rural representation of Nakaseke district. These sub-counties will be appropriate for implementation of the study due to excellent working relationships with the local communities through prior work; they do not currently have these kinds of interventions being implemented and have a rising number of NCD cases. Nakaseke sub country has an estimated total population of 21,500 people, with 4392 households, 6 parishes, and 41 villages, Nakaseke town council has an estimated total population of 9100 people with 1992 households; with 5 parishes and 17 villages and Kasangombe has an estimated total population of 26,600 people with 4851 households, with 4 parishes and 44 villages [17].

### Study population

The study population will include: participants with hypertension (systolic > 140 and/or diastolic > 90) attending the two NCD clinics, adults 18 years and above, participants residing in the three sub counties (Nakaseke Town Council, Nakaseke Sub County, and Kasangombe of Nakaseke district), and participants able to give informed consent. Patients diagnosed with hypertension but already controlled will be excluded. Pregnant women and patients with an expected life expectancy of less than one year will be excluded from participating in the study.

### Study design

The study will employ a closed cohort, superiority stepped wedge cluster randomized design. There will be a sequential crossover of clusters from the control to the intervention arms and the order of the cross over will be randomly determined (Fig. 1). This study will be conducted in 21 clusters within Nakaseke district. Each cluster will consist of 4–5 villages (Table 1). Participant recruitment will occur before randomization. At the beginning of the study period, we will collect baseline demographic data from each of the participants. All the villages within the study will eventually receive the intervention, thereby improving equity and acceptability. To minimize contamination, we will ensure that clusters are well separated to minimize social contact between participants in the intervention and control arms. Since all clusters will be observed under both the intervention and control arm, we anticipate that imbalances are less likely to occur. To further address the issue of contamination, individuals within the same cluster will be randomized to receive the intervention at the same time. Also, since the study will be conducted in a rural population, we expect adjacent neighborhoods to be far apart from each other, and this could additionally reduce the rates of contamination within the study area. In addition, CHW activities are directed to individuals at the level of the home and not large community groups or gatherings. This should decrease exposure of non-enrolled patients from outside randomized clusters to the interventions. We plan to rollout the intervention in two clusters per month and one cluster in the final month (Fig. 2).

**Fig. 1 Fig1:**
[figure not shown]
Recruitment design

**Table 1 Tab1:** Formation of clusters within Nakaseke district

Sub county	No. of villages	No. of clusters
Nakaseke Town Council	17	4
Nakaseke Sub County	41	8
Kasangombe	44	9
Total	102	21

**Fig. 2 Fig2:**
[figure not shown]
Schedule of enrollment and assessment of participants

### Ethical considerations

The trial protocol was approved by the institutional review board (IRB) at the Makerere University College of Health Sciences School of Biomedical Sciences (SBS-2021-53) and the Uganda National Council of Science and Technology (HS1917ES). The trial was also registered with ClinicalTrials.gov (Identifier: NCT05068505) on October 6, 2021. Prior to any data collection, research staff will explain study purpose and procedures to participants. Written informed consent will be obtained for this and future ancillary studies, if applicable, from all the study participants prior to taking part in the study. In situations where a participant is unable to read or write, a thumbprint will be obtained, along with written signature from a witness. Access to identifiable individual-level data will be restricted to the study team. Protocol amendments will be approved by all regulatory parties prior to change in research activities. CHWs, research assistants, and the project team will also be trained in Good Clinical Practice and Protection of Human Research Participants.

### Training and quality control

The principal investigator (PI) and the project manager will conduct an all-study personnel-training session on the study protocol and Standard Operating Procedures before the initiation of the study. The research team will also be required to train in Good Clinical Practice, Human Subject Protection, and Responsible Conduct of Research. We will file copies of these research certificates in the investigation file. The PI will hold biweekly meetings with all the field staff and monthly meetings with all the investigators for their input and ensure that the study sticks to the study protocols and Standard Operating Procedures. The data will also be captured using tablet computers programmed with Research Electronic Data Capture (REDCap; Vanderbilt University, Nashville, USA). The study team will hold bi-monthly meetings to obtain continued support from the international partners from USA and Europe. The PI will also hold biweekly meeting to ensure that the study team sticks to the proposed study protocols.

### Community health worker training

A 5-day training will be held following the pre-established NCD curriculum for CHWs. Ministry of Health (MOH) village health team trainers will train CHWs in health promotion, basic research ethics, quality assurance, and control and use of tablet computers/redcap software. CHWs will also be trained in hypertension, screening risk factors, referral criteria, and need for community follow-up. Refresher training will be performed after 6 months.

### Logistic support

After the training, the CHWs will be equipped for their role with face masks, gloves, face shields, rain coats and gumboots, BP machines, weighing scales, tablet computers, glucometers, glucose strips, and urine dipsticks. They will also be remunerated with a monthly stipend.

### Recruitment, enrollment, and retention

Research assistants, who will obtain informed consent and collect the baseline and three-monthly data, will enroll study participants from the NCD clinics. Participants will be contacted by the CHWs, prior to the intervention rollout to schedule an initial home visit. The baseline assessment will be conducted following the WHO’s STEPwise approach to surveillance, a standard method for analyzing risk factors for NCDs, such as data collection on risk factors using the questionnaire and bio-physical measurements [18].

### Clustering and randomization

There will be a sequential crossover of clusters from the control to the intervention arms and the order of the cross over will be randomly determined. Participants will be recruited before randomization and the person responsible for the recruitment will be blinded from the allocations of interventions to the different clusters. The unit of randomization will be a cluster of 3-4 adjacent villages. A list of all villages from the three sub counties is available, and a total of 21 clusters will be designed from the three sub counties (Table 1). Clusters will be randomly assigned to the eleven phases of intervention rollout. Details of the timing of cluster allocation and randomization will be maintained in a secure document available to the project manager and PI and unavailable to those who enroll. The investigators and the participants will not know what groups will be randomized before allocation of the intervention. Because it is a CHW-led intervention, study investigators and participants cannot be concealed after enrolling. The allocation sequence will be randomly generated using a computer by our statistician and will be provided to the project manager at the time of enrollment of a new cluster.

### Primary outcome

Decrease in the average systolic pressure between the intervention and control arms.

### Secondary outcomes

Proportion of participants with blood pressure control, defined as blood pressure < 140/90. Glycemic control defined as a reduction > 1 in HbA1C. Composite negative clinical CVD outcomes including CVD related admissions, stroke, myocardial infarction, and incident heart failure will also be assessed as secondary variables. We will additionally measure quality of life through the EuroQol-5D-5L [19]. We will measure effectiveness measures including adoption and fidelity to the intervention over time.

### Independent variables

• Sociodemographic characteristics of the participants such as age, sex, education level, and marriage status

• Life style characteristic on: diet, tobacco use, and alcohol consumption

• Medical history including family history on NCDs such as diabetes, hypertension, and other co-morbidities like HIV and CKD

### Sample size determination

The primary outcome will be a change in systolic blood pressure between the intervention and control group. To compute the required sample size for the step wedge design, we first computed the required sample size if we were to implement an individual randomized trial. By conservative estimates, we estimate a 6-mmHg difference in systolic blood pressure between the intervention and control group [20, 21]. Accounting for the stepped-wedge design and constant cluster sizes (40) within the sample, with a fixed number of clusters (*n* = 21) and a power of 90%, at 0.05% level of significance, a sample size of 869 will power the study to detect an absolute minimally important clinical difference (MCID) of 6 mmHg in the mean systolic blood pressure between the intervention and control arms. We intend to roll out the intervention within two clusters each month and within one cluster during the final month.

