## Discussion

We discuss the rationale, methods, and protocols for the CHW-HTC closed cohort stepped wedge cluster randomized trial in Uganda. The overall goal of the trial is to evaluate the effectiveness of a CHW-led intervention in blood pressure control among confirmed hypertensive patients in a rural Ugandan community. Based on our statistical power calculations, we will work with a fixed number of 21 clusters, enrolling 40 participants in each cluster. Similar studies have proven applicability across various settings, strengthening our theory-informed approach. A number of studies show that CHWs can be effective in delivering patient management strategies. A randomized controlled trial based in Nepal proves that a female community health worker intervention could effectively reduce mean systolic blood pressure in hypertensive patients [26]. A Mexican-based study indicates that a CHW-led intervention among hypertensive or diabetic patients is associated with a twofold increase in the odds of disease control [27]. Similarly, a CHW-led intervention in the USA to improve hypertension management among Filipino Americans with uncontrolled blood pressure finds that blood pressure was controlled at a significantly greater percentage among the treatment group participants (83.3%) compared to the control group (42.7 %) [21].

We will follow 11 phases of implementing the intervention, introducing it within two clusters at each step of the trial and within one cluster in the final step (Fig. 2). Clusters will be assigned randomly to intervention rollout while one CHW will be attached to each cluster. We will center our intervention on monthly pro-active household visits by trained CHWs over a study period of 1 year. A local non-government organization and a multinational research group with wide-ranging experience in conducting research in rural communities will carry out the study. The local coordination will support overcoming economic and cultural barriers to enrollment and support the establishment of community trust. This clinical trial builds upon previous research and collaborations in LMIC settings investigating the advantages of engaging CHWs in the patient-centered management of hypertension.

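### The stated total (869), the only significance level (0.05%) and the villages per cluster (3-4) do not agree with the rest of the article; minor text corrections

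*Protocol article*

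**What the plan says.** All references are to the protocol article.

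- **Cluster size and number.** Sample size determination starts from a fixed 21 clusters and this condition: "Accounting for the stepped-wedge design and constant cluster sizes (40) within the sample". The Discussion restates it: "we will work with a fixed number of 21 clusters, enrolling 40 participants in each cluster". Study design also gives 21 clusters: "This study will be conducted in 21 clusters within Nakaseke district".
- **Total, power and level.** The same sentence in Sample size determination concludes: "a power of 90%, at 0.05% level of significance, a sample size of 869 will power the study". The target difference is 6 mmHg in mean systolic pressure. The Abstract repeats the total: "stepped-wedge cluster randomized controlled trial study of 869 adult patients with hypertension". No other section gives a significance level.
- **Randomised unit.** Clustering and randomization: "The unit of randomization will be a cluster of 3-4 adjacent villages". Study design: "Each cluster will consist of 4–5 villages (Table 1". Table 1 lists 17 villages in 4 clusters (Nakaseke Town Council), 41 in 8 (Nakaseke Sub County) and 44 in 9 (Kasangombe), in all 102 villages in 21 clusters. Study setting also gives 102 villages.

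**The concern.** These three items define the trial: how many people to recruit, what counts as significant, and what is randomised. As printed they cannot all be true.

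A recruiter who stops at 40 per cluster ends 29 short of 869. A recruiter who aims for 869 breaks the constant size of 40. The printed level is a hundredth of the conventional 5%, and nothing else in the article corrects it. It matters outside the sample size too, because Data monitoring attaches a rollout decision to a statistically significant difference and names no level of its own. A unit of 3-4 villages cannot cover the villages that the article says are in the study.

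**Working it through.** **1. Total sample size**

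Inputs: 21 clusters, 40 per cluster and a total of 869 (Sample size determination; Discussion; Abstract).

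- Product: 21 × 40 = 840, so 869 is not reproduced.
- Gap: 869 − 840 = 29, and 29/869 = 3.3%.
- Implied cluster size: 869/21 = 41.38. No constant whole number gives 869, since 21 × 41 = 861 and 21 × 42 = 882.
- Usual attrition allowances do not bridge the gap: 840/(1 − 0.05) rounds up to 885, and 840/(1 − 0.10) rounds up to 934. An allowance of about 3.3% would give 869 (840/0.967 = 868.7), but none is stated.

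Effect on power, assuming that 869 gives 90% at two-sided 5% and that information is proportional to the number of participants:

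- Standardised effect at 869: 1.960 + 1.2816 = 3.2415 (from unrounded values).
- At 840: Φ(3.2415 × √(840/869) − 1.960) = Φ(1.227) = 0.890.

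The loss is about one point.

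The full calculation behind 869 cannot be re-run, because the article gives no standard deviation or intra-cluster correlation. An article may leave those to the full protocol, so this is not counted against it.

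**2. Significance level**

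Input: 0.05%, that is alpha = 0.0005, with 90% power (Sample size determination). Sidedness is not given.

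To show what the printed level would mean, take a design with 90% power at two-sided 5% and test it at two-sided 0.0005 (critical value 3.4808):

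- Power: Φ(3.2415 − 3.4808) = Φ(−0.239) = 0.405, about 41%.
- Information needed to regain 90%: ((3.4808 + 1.2816)/3.2415)² = 2.16 times as much.

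The standardised effect is fixed by the assumed 90% at 5%, so neither a standard deviation nor a correlation is needed.

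**3. Villages per cluster**

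Inputs: Table 1.

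| Sub-county | Villages / clusters | Mean |
|---|---|---|
| Nakaseke Town Council | 17/4 | 4.25 |
| Nakaseke Sub County | 41/8 | 5.125 |
| Kasangombe | 44/9 | 4.89 |
| All | 102/21 | 4.86 |

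- At 3-4 villages, 21 clusters hold 21 × 3 = 63 to 21 × 4 = 84 villages, which leaves at least 102 − 84 = 18 unplaced.
- All three sub-county means exceed 4, so 3-4 fails in every sub-county.
- At 4-5 villages, Town Council (16 to 20) and Kasangombe (36 to 45) fit. Nakaseke Sub County does not: 8 × 5 = 40 is less than 41, so at least one cluster there has 6 or more villages.

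**The case against.** The best defence is that these are reporting slips with little consequence, and most of it stands.

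- **The level.** 0.05% is most likely 0.05 with a stray percent sign, in which case power is unaffected. If it was literal, the 90% may have been computed at that level. For example, ignoring the stepped-wedge adjustment, an individually randomised total of 869 with a 6 mmHg difference has 90% power at 0.0005 if the standard deviation is 6 × √(869/4)/4.7624 = 18.6 mmHg, and at 5% if it is 6 × √(869/4)/3.2415 = 27.3 mmHg. The article gives nothing to decide between them. A reader might infer that the trial has only 41% power. The documents do not support this: the figure requires power to be set at 5% and the test then run at 0.0005, and nothing in the article says so.
- **The total.** Forty may be a rounded planning input and 869 the output of the calculation. That is possible, but the article calls 40 constant and nowhere mentions rounding or an allowance. The contradiction remains, at a cost of about one point of power.
- **The villages.** Villages per cluster do not enter a calculation based on participants, and 4-5 is a fair summary of a mean of 4.9. Both are true. The figure in Clustering and randomization is still incompatible with Table 1, and that section defines the randomised unit.

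**Conclusion.** The concern holds as a set of minor text errors. The total contradicts the stated clusters by 29 participants (3.3%), or about one point of power if 869 gives 90% at two-sided 5%. The sole significance level is wrong as printed, assuming that 5% was meant; the 41% shows how far the printed level departs from convention and is not an estimate of this trial's power. The 3-4 village unit contradicts both Study design and Table 1, and this rests on the article's own counts alone.

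A reader might also infer that the 90% is invalid because rollout is monthly while the Abstract says "We will measure blood pressure at baseline and 3-monthly for the entire cohort". The documents do not support that. Sample size determination mentions months only in describing the rollout and never says that the calculation assumed monthly measurement. Any recalculated power would rest on a standard deviation and correlations that the article does not give. Nothing here shows the trial to be underpowered.

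**What to change.** 1. In Sample size determination, state the significance level as 5% (0.05), with its sidedness, if that was intended.
2. Give one total throughout the Abstract, Sample size determination and Discussion. Either use 840 (21 × 40) with the power restated, or keep 869 and replace the constant 40 with a mean of 41.4 per cluster or the allowance that produces 869.
3. Describe the cluster identically in Study design and in Clustering and randomization, in line with Table 1. Table 1 prints no range, so state the range actually formed, noting that its counts force at least one cluster of 6 or more villages in Nakaseke Sub County.

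The cost is a text correction, plus one re-run of the power calculation if 840 is chosen. It needs no patients beyond the 869 already planned.
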